## Abstract

**Background:**

Public speaking anxiety (PSA) significantly impairs academic and professional outcomes among university students. While virtual reality exposure therapy (VRET) shows promise for PSA treatment, the specific contribution of social and emotional interviewer reactions remains unclear. This study examines whether VRET with graded interviewer reactions leads to greater reduction in public speaking anxiety than standard automated VR exposure.

**Methods:**

This two-arm, parallel-group, superiority randomized controlled trial will recruit 92 Korean university students aged ≥18 years with elevated PRPSA (Personal Report of Public Speaking Anxiety-18 ≥ 58). Participants will be randomized 1:1 to receive either VR interview training with graded interviewer reactions or control VR training with automated voice prompts only. The intervention consists of three VR sessions, with assessments conducted at baseline, immediately after each session, and at 6- and 12-week follow-ups. The primary outcome is change from baseline in Public Speaking Anxiety Scale (PSAS) total scores at each post-baseline assessment occasion, analyzed using a linear mixed-effects model including fixed effects for group, assessment occasion, and their interaction. Secondary outcomes include Liebowitz Social Anxiety Scale–Self Report and Fear of Negative Evaluation–Brief scores, as well as physiological indicators reflecting anxiety responses during VR exposure, including heart rate variability and electrodermal activity. Exploratory analyses will examine behavioral synchrony using motion energy analysis of video recordings and acoustic features of speech to capture anxiety-related movement and vocal patterns.

**Discussion:**

This trial addresses the limited evidence regarding the added value of graded interviewer reactions in VRET for public speaking anxiety by examining whether they improve outcomes beyond those achieved with standard automated VR exposure. The findings may clarify the role of socially responsive feedback in virtual exposure and inform the development of VR-based anxiety interventions.

**Trial registration:**

Clinical Research Information Service (CRiS) KCT0011111. Registered on 06 November 2025.

**Supplementary Information:**

The online version contains supplementary material available at 10.1186/s13063-026-09779-0.

## Background

Recognized as one of the most prevalent fears in the general population, Public Speaking Anxiety (PSA) has been shown through extensive research to rival or even surpass the fear of death among Americans [1]. The Diagnostic and Statistical Manual of Mental Disorders, Fifth Edition (DSM-5), includes a performance-only specifier for social anxiety disorder, addressing cases in which anxiety manifests exclusively in evaluative situations [2]. When PSA becomes chronic, the risk of progression to generalized social anxiety disorder increases substantially [3]. In such clinically meaningful cases, PSA extends beyond a simple emotional response to encompass avoidance behaviors, physiological hyperarousal, and cognitive interference [4].

Building on this clinical understanding, past research emphasizes that PSA is particularly pronounced among university students worldwide, representing one of the most common psychological difficulties experienced in academic settings [5, 6]. PSA can have a pronounced and enduring negative impact on students’ academic performance and later professional success [7] and has been identified as a clinically significant concern among healthcare professionals [8]. Moreover, this anxiety often persists beyond the academic environment, manifesting in other social-evaluative contexts that demand self-presentation, such as job interviews. It directly influences students’ transition into the working world, where interview anxiety emerges as a particularly significant barrier in employment processes. Job interviews represent a prototypical PSA situation [9], exemplifying high-stakes contexts in which social performance abilities are directly evaluated by interviewers [10]. Applicants with elevated interview anxiety often display anxious non-verbal behaviors during interviews, which may negatively influence interviewer evaluations and subsequently affect hiring decisions [11, 12]. These effects extend beyond individual career development, adversely impacting organizational talent-selection processes [13].

To counter these detrimental effects of anxiety, practitioners supported by extensive research and clinical evidence have identified exposure therapy as the most effective intervention for interview anxiety [14]. Operating on the principle of reproducing actual performance situations to elicit realistic anxiety responses, this re-enactment of the event gradually reduces anxiety through systematic desensitization achieved via repeated exposure [15].

However, traditional in vivo exposure therapy is constrained by several limitations, including high costs, time requirements, and psychological burden, which may restrict its practical application in clinical decision-making [16]. These barriers have been increasingly addressed through rapidly advancing virtual reality (VR) technology [17]. VR exposure therapy (VRET) represents an innovative treatment approach capable of inducing anxiety levels comparable to real situations, while enabling repeated exposure in safe, controlled environments, thereby effectively overcoming the primary barriers associated with traditional methods. The actual effectiveness of VRET has been empirically supported by recent meta-analytic research. In particular, a meta-analysis conducted by Reeves et al. (2022), which analyzed seven studies comprising 341 participants, demonstrated that VRET produced large effect sizes for PSA reduction compared with control groups (*d* = −1.39, 95% CI = −2.08 to −0.70, *Z* = 3.96, *p* < 0.001) [18]. Importantly, this effect size closely approximated that of traditional in vivo exposure therapy (*d* = −1.41), suggesting that VRET offers comparable clinical utility and may serve as a viable alternative to conventional methods [18].

Regarding VR intervention research targeting interview situations, recent studies have shown promising outcomes. General VR-based presentation training research has reported large effect sizes, stabilization of physiological indicators such as heart rate variability, and improvements in presentation behaviors [19]. Furthermore, research on Virtual Reality Job Interview Training (VR-JIT), specifically designed for employment preparation, has presented not only reductions in interview anxiety but also enhancements in interview skills and increased actual employment rates [20, 21]. These findings reflect high ecological validity, and indicate that VRET can extend beyond simple anxiety reduction to produce tangible functional improvements in job interview performance.

Despite the growing body of VR interview intervention research, existing studies have focused primarily on quantitative variables (such as audience size, presentation venue scale, and distance from the audience) to validate anxiety induction and intervention effects, while omitting social presence, which has been shown to constitute a core element of VRET [22]. Some studies have incorporated social interactions, such as ambiguous or negative audience feedback [23], without determining whether these factors enhance intervention effectiveness [24]. Nevertheless, systematic research on qualitative factors, including interviewers’ emotional and social reactions, remains considerably limited. Graded reaction difficulty adjustments (from positive to neutral to negative) have only been mentioned exploratorily [25], and systematic comparative studies are still lacking.

In addition, exploration of connections between physiological indicators and actual behavioral changes remains insufficient. Recent research reveals significant gaps in understanding how physiological arousal translates to observable behaviors in PSA contexts. Gallego et al. (2022) found that while autonomic indicators are frequently elevated in high-anxiety individuals, “the evidence linking these physiological markers to observable behavioral changes is mixed and often inconsistent,” showing considerable individual variability, where some exhibit high physiological activation without corresponding behavioral changes [4].

Since PSA usually manifests through visually observable behaviors (e.g., gesturing and head movements), objective measurement of these behaviors is necessary. In particular, auditory dimensions, representing an important behavioral component and manifesting through voice tone and vocal tremor, have revealed that anxiety fundamentally reorganizes vocal parameters, with jitter identified as the sole speech parameter consistently linked to the anxiety state. Most voice analysis research has been conducted in controlled laboratory settings with limited ecological validity, focusing on isolated parameters while overlooking the complex interrelationships among vocal features.

In addition, behavior encompasses acoustic and prosodic dimensions, including pitch dynamics, loudness modulation, pause structure, and speech rate [26]. Recent findings have suggested that anxiety reorganizes the multivariate relationships among vocal parameters, rather than producing stable shifts in single acoustic features. Among these parameters, jitter, which quantifies micro-level irregularities in vocal fold vibration, has frequently emerged as a central feature associated with anxious arousal within network-based analyses [27]. However, findings across studies are not entirely consistent, indicating that the role of jitter should be interpreted within the broader interdependence of acoustic features rather than as a standalone marker [27].

Jitter estimation requires highly controlled recording and analysis procedures to ensure measurement reliability, and such methodological sensitivity makes it less feasible in naturalistic speech contexts [28]. Accordingly, the present study has focused on higher-level prosodic features (e.g., pitch variability, loudness modulation, and temporal fluency), which have been repeatedly identified as salient cues of expressive behavior under ecologically valid communicative conditions [26, 28]. Previous voice analysis research has primarily relied on controlled laboratory tasks using acted or scripted speech, often emphasizing isolated acoustic parameters while neglecting higher-order temporal dynamics and inter-feature dependencies [27, 28]. These methodological limitations underscore the need for multimodal frameworks that integrate physiological markers, behavioral synchrony, and prosodic vocal behavior within ecologically valid communicative settings, a direction increasingly emphasized but still underexplored in public speaking anxiety research [28].

Recent studies have furthermore reported that, in social interaction situations, not only individual movements but also bidirectional synchronization with interaction partners correlate with social anxiety states [29]. A deeper understanding is needed of how such synchronization levels relate to anxiety induction and intervention effects in interview situations. This area has not yet been systematically investigated in PSA intervention research. Therefore, these limitations highlight the need for multimodal approaches that examine physiological markers, behavioral synchronization, and vocal characteristics within ecologically valid VR contexts.

This study employs a randomized controlled trial (RCT) to investigate how the presence or absence of interviewers’ social and emotional reactions in interview situations affects participants’ short-term anxiety induction and long-term intervention effects. The primary objective is to test whether VRET with graded interviewer reactions produces greater reductions in public speaking anxiety than standard automated VRET. Specifically, through multidimensional analyses of PSA-related self-report scales and physiological and behavioral indicators between groups, we seek to comprehensively examine how interviewer reactions in interview situations influence intervention effectiveness. We hypothesize that participants assigned to the graded-reaction intervention will show greater improvement in public speaking anxiety across prespecified assessment occasions than those assigned to the control condition.

## Methods

### Trial design

This study is a two-arm, parallel-group, superiority randomized controlled trial with 1:1 allocation, comparing PSA improvement between VR presentation simulations incorporating interviewers’ social and emotional reactions and VR presentation simulations without interviewer reactions [30]. Repeated assessments will be conducted over 12 weeks, including baseline, post-session assessments after each of the three intervention sessions, and 6- and 12-week follow-ups.

### Participants

This study will be conducted with students from a single university in Ulsan who report PSA. Participants will be recruited through promotional posters within the university and online community promotional posts. Students wishing to participate will first complete online self-screening to assess preliminary inclusion and exclusion criteria. Participants must be university students aged 18 years or older, native Korean speakers, with Personal Report of Public Speaking Anxiety-18 (PRPSA-18) scores of 58 points or higher [31]. The PRPSA-18 is an 18-item empirically developed scale designed to screen individuals with elevated public speaking anxiety levels. The 58-point cutoff represents the optimal criterion for distinguishing high PSA [31]. Exclusion criteria include individuals currently receiving treatment for PSA or social anxiety disorder, those receiving psychiatric diagnosis and medication treatment, individuals diagnosed with major depressive disorder, panic disorder, or agoraphobia, those at risk for suicidal ideation, and individuals with VR usage limitations (visual impairment, severe dizziness, etc.). Those who are eligible will be invited to the laboratory, where a study investigator will explain the study, confirm eligibility, and obtain written informed consent. After enrollment, participants will be randomized in a 1:1 ratio to one of the two study arms. Baseline assessment (T0) will then be conducted before the first intervention session, after which participants will proceed to the intervention and subsequent follow-up assessments. Expected demographic characteristics of the study population are summarized in Table 1.

**Table 1 Tab1:** Summary table of demographic participant characteristics for a protocol

Non-clinical participant characteristics	
Characteristics	The people we would expect to see included
Age	Mean age 20–22 years (range 18–25 years). The average age of Korean university students is 18–19 years for freshmen, with most enrolled students expected to be distributed in their early twenties [32]
Sex	Given the predominantly male composition of the science and engineering student population (73.3% male, 26.7% female), and evidence that public speaking anxiety is typically higher among females [33], the gender distribution of the study sample is expected to be more balanced
Gender	Most participants are expected to have gender identity consistent with sex assigned at birth
Race, ethnicity and ancestry	Limited to native Korean speakers according to inclusion criteria to ensure cultural and linguistic homogeneity
Socioeconomic status	Expected to be predominantly middle class. The socioeconomic background of university students in the Ulsan region is at a moderate level, with most predicted to fall within the household income range of 4–6 million KRW per month [33]
Geographic location	Predominantly residents of Ulsan Metropolitan City and nearby Gyeongsangnam-do region

### Sample size

The primary outcome is public speaking anxiety as measured by the PSAS, assessed at six prespecified assessment occasions (baseline; immediately after each of the 3 sessions; 6- and 12-week follow-ups). The study is powered to detect a group-by-assessment-occasion interaction reflecting between-group differences in change from baseline in PSAS across repeated assessments.

Previous meta-analyses demonstrate that VRET produces large effects versus waitlist conditions (*g* = 0.90) and shows comparable efficacy to in vivo exposure therapy [16, 34]. However, since both groups in the present trial receive active PSA training, we anticipated only a small incremental effect. Our intervention extends standard VR exposure by introducing graded interviewer reactions delivered as sequential components of a single exposure package. Research indicates that social-evaluative characteristics of virtual audiences can influence performance confidence and anxiety responses, with some improvements transferring to real-world public speaking performance [25, 34].

Based on these findings, a conservative effect size of *f* = 0.15 was assumed for between-group differences in repeated outcome change. A priori power analysis using G*Power (ANOVA: repeated-measures, within-between interaction; *α* = 0.05, 1 − β = 0.80, two groups, six measurements, correlation among repeated measures = 0.50, nonsphericity correction *ε* = 0.50) indicated a total sample of *N* = 78. Although the primary analysis will use a linear mixed-effects model, the sample size was calculated using a repeated-measures ANOVA framework focusing on the group-by-assessment-occasion interaction. This interaction corresponds to the primary estimand of interest and aligns with the primary analysis model. The ANOVA-based approach was adopted as an approximation because prior data were insufficient to parameterize variance components required for LMM-based simulation. To account for approximately 15% attrition commonly observed in VR exposure studies [35], the recruitment target was set at 92 participants (46 per group). Figure 1 shows the CONSORT flow diagram for the recruitment process.

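### The sample size labels f = 0.15 small and conservative, but for a same-sign difference it means a peak group difference of at least 0.60 SD

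*Protocol article*

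**What the plan says.** The Sample size section of the protocol article first gives a reference point: "VRET produces large effects versus waitlist conditions (*g* = 0.90"). It then argues downward from it: "since both groups in the present trial receive active PSA training, we anticipated only a small incremental effect". The figure used is "a conservative effect size of *f* = 0.15 was assumed for between-group differences in repeated outcome change".

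That f goes into the G*Power routine "ANOVA: repeated-measures, within-between interaction", with alpha 0.05, power 0.80, two groups, six measurements and "correlation among repeated measures = 0.50, nonsphericity correction *ε* = 0.50". The result is 78 in total, raised to 92 (46 per group) for about 15% attrition. The section says the trial is powered for the group-by-occasion interaction and that this interaction corresponds to the primary estimand. It does not convert f = 0.15 into PSAS points or a standardised mean difference, and it gives no expected pattern of the group difference over T0–T5.

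**The concern.** The section contrasts a large effect against waitlist with a small one expected here, because both arms are active, and presents f = 0.15 as the cautious expression of the small one. In a plain two-group comparison f = d/2, so 0.15 would be d = 0.30 and the label would be fair. In the within-between interaction routine, f measures the spread of the group difference across occasions, and the same 0.15 then stands for a much larger difference at its peak.

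At stake is what the 80% refers to. If it holds only for differences well above what the text calls small, the stated power is not the power for the effect that the plan says it anticipates.

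**Working it through.** **Inputs** (all from the Sample size section): f = 0.15, alpha = 0.05, k = 2 groups, m = 6 measurements, rho = 0.50, epsilon = 0.50, N = 78, attrition 15%.

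**1. Reproduce the plan's figure.** With the routine's default definition of f:

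- lambda = f² · N · m · epsilon / (1 − rho) = 0.0225 · 78 · 6 · 0.5 / 0.5 = 10.53
- df1 = (k − 1)(m − 1) · epsilon = 2.5; df2 = (N − k)(m − 1) · epsilon = 190
- power = 0.801 at N = 78 and 0.790 at N = 76, so 78 is the smallest even N
- 78 / 0.85 = 91.8, rounded up to 92

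Both figures are right. G*Power's two other effect-size options would need about 186 and 188, so the stated 78 identifies which definition of f was used: the SD of the interaction effects divided by the within-cell SD.

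**2. Translate f.** Let d_t be the group difference at occasion t in SD units. With two groups the interaction effects are ±(d_t − mean d)/2, so

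f = SD_pop(d_t) / 2, and f = 0.15 means SD_pop(d_t) = 0.30 over the six occasions.

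At rho = 0.50 the SD of change from baseline is sqrt(2(1 − 0.50)) = 1 raw SD, so d_t is also in SDs of change. A simulation of a constant 0.805 SD difference under equal correlations gave power 0.959, against 0.960 from the formula with epsilon = 1, which confirms the mapping.

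**3. Apply it to time profiles with d = 0 at T0.** The profiles are assumed, since the document gives none. Peak = 0.15 / (f per 1 SD of peak).

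| Profile | f per 1 SD of peak | Peak for f = 0.15 | Average over T1–T5 |
|---|---|---|---|
| T3–T5 only | 0.2500 | 0.60 SD | 0.60 × 3/5 = 0.36 SD |
| T4–T5 only | 0.2357 | 0.64 SD | 0.636 × 2/5 = 0.25 SD |
| Constant T1–T5 | 0.1863 | 0.81 SD | 0.81 SD |
| Linear over occasions | 0.1708 | 0.88 SD | 0.878 × 0.6 = 0.53 SD |

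A population SD cannot exceed half the range, so SD_pop = 0.30 forces a range of at least 0.60 SD. With d = 0 at T0 and no change of sign, the range is the peak, and 0.60 SD is its floor. Against the quoted 0.90, these peaks run from 0.60/0.90 = 67% to 0.88/0.90 = 98%.

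**4. Power for a small difference.** The document does not define small as a mean difference; a peak of 0.30 SD is assumed. With N = 78, rho = 0.50 and epsilon = 0.50, lambda = 468 · f²:

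| Profile | f at peak 0.30 SD | lambda | Power | Power, epsilon = 1 |
|---|---|---|---|---|
| T3–T5 only | 0.0750 | 2.63 | 26% | 38% |
| T4–T5 only | 0.0707 | 2.34 | 23% | 34% |
| Constant T1–T5 | 0.0559 | 1.46 | 16% | 21% |
| Linear | 0.0512 | 1.23 | 14% | 18% |

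With all 92 retained and epsilon = 0.50, the range is 16–30%. At a peak of 0.50 SD and N = 78 it is 33–63%, or 48–85% with epsilon = 1.

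**The case against.** Several objections have force.

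- **Nothing is miscalculated.** This stands. A reader might infer that 78 or 92 is wrong; both reproduce. The fault is in the description of the effect.
- **The 0.60 SD floor is conditional.** It bounds the range of the difference, which equals the peak only if the sign never changes. The Background says the trial studies short-term anxiety induction as well as longer-term effects, and only the experimental arm meets negative reactions in session 3, so a crossing profile is conceivable. If the experimental arm were better at T1, equal at T2, worse at T3 and better at T4–T5, f = 0.15 would need only 0.40 SD at any occasion. Worse at T3 and better at T4–T5 would need 0.44 SD. At 0.30 SD those two profiles have 53% and 46% power. This limits the claim, but the stated hypothesis of greater improvement across occasions points to same-sign profiles.
- **A peak is not an average.** The Primary outcome section defines the estimand as a difference in mean change across the post-baseline occasions. Read as a T1–T5 average, the same f is 0.25–0.81 SD. It would be wrong to say that the trial can detect only an average difference of 0.6–0.9 SD.
- **Epsilon and rho matter.** Equal correlations of 0.50 imply sphericity, so epsilon = 0.50 is a real cautious allowance. The text, however, attaches the word conservative to f. If rho were 0.70 (assumed) with epsilon = 1, then for 0.30 SD lambda = f² · 78 · 6 / 0.30 is 4.09 (linear) to 8.77 (T3–T5), with power of 29–60%: better, still short of 80%.
- **A null result need not be misread.** The Discussion comments only on a significant interaction, so how a null would be interpreted is not in the document, and the point does not depend on it.

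**Conclusion.** The point holds as one about how the effect is described. N = 78 and 92 are correct for f = 0.15. For arms equal at T0 and a difference of one sign, that f requires a peak group difference of at least 0.60 SD, and about 0.6–0.9 SD over the profiles tabulated. This does not fit *small* or *conservative* beside a g of 0.90 that the same section calls large. For a 0.30 SD difference the planned interaction test has about 14–26% power with the plan's inputs (18–38% at epsilon = 1), so the stated 80% does not apply to it.

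The result rests on assumed time profiles, on 0.30 SD as the meaning of small, and on rho = 0.50. A reader might go further and conclude that the trial is underpowered for its primary estimand. The document does not support that: it names no single-degree-of-freedom contrast for the average change, so the power of such a contrast cannot be read from the plan.

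**What to change.** In the Sample size section:

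1. Delete *small* and *conservative* as descriptions of f = 0.15.
2. State the time profile assumed for the group difference over T0–T5.
3. State that 78 completers give 80% power by the interaction test for a peak difference of about 0.6–0.9 SD under same-sign profiles, and give the T1–T5 average that goes with the chosen profile (for example 0.81 SD if constant, 0.53 SD if linear, 0.36 SD if T3–T5 only).
4. If the authors intend one contrast for the estimand in the Primary outcome section, such as average change over T1–T5, name it and report its own detectable difference.

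Keep N = 92. The cost is one paragraph and a less favourable stated figure; no participants are added and no analysis has to change.
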